### Data analysis

Primary outcome of the study is the effect of 6-month exercise training on maximal aFID and vFID in the HIIT group compared to the control group. Descriptive statistics (mean, standard deviation) will be used to describe baseline and follow-up characteristics. Normal distribution of data will be tested by means of Shapiro-Wilk test. To analyze intervention effects after 6 months, we will use an analysis of covariance (ANCOVA) according to the intention-to-treat principle to compare differences in primary and secondary endpoints between HIIT and control group, corrected for the corresponding baseline value and main confounders. Boxplots will be used to visualize primary and secondary endpoints before and after the 6-months exercise intervention. If the fraction of missing values exceeds 5%, we will account for missing data using multiple imputation. A multiple linear regression model, adjusted for covariables as age and sex, will be used to describe the association between the delta change of retinal microvascular adaptations and the delta change of classical risk factors such as VO_2_peak, BMI, systolic and diastolic BP, fasting glucose, serum lipids, hs-CRP, inflammatory and oxidative stress markers as well as BDNF. Changes in glaucoma therapy may coincide with the course of this project, as the trial does not interfere with routine glaucoma management. Therefore, there is a particular need to correct for therapy changes in the statistical analysis. Any changes in therapy will be included as separate variables. Any step-up of therapy, being either surgery, laser trabeculoplasty or additional drops, will be coded as a binary, summarizing variable (yes/no) and as separate variable (quantifying total number of drops, total number of surgeries). Model assumptions will be checked graphically using residual diagnostic plots. All statistical tests will be two‐sided and the significant level is set to 0.05.

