#### Secondary

• To investigate whether 6 months of exercise training improve CRAE and CRVE diameters in glaucoma patients compared to the control group.• To investigate whether 6 months of exercise training improves PWV as a marker of large artery stiffness in glaucoma patients compared to the control group.• To investigate retinal aFID and vFID, other flicker light derived markers, as well as retinal CRAE and CRVE after 6 months of exercise training and a further 6 months of self-maintenance exercise training as compared to the control group at 12 months.• To investigate large artery FMD and PWV after 6 months of exercise training and a further 6 months of self-maintenance exercise training as compared to the control group at 12 months.• To investigate whether 6 months of exercise training increase brain-derived neurotrophic factor (BDNF) levels and reduce inflammation as well as oxidative stress in peripheral blood. To assess IOP, use of IOP lowering eye drops and occurrence of laser trabeculoplasty or surgical interventions after six and 12 months in the intervention group as compared to the control group.• To assess Optical Coherence Tomography (OCT) and visual field metrics at six and 12 months in the intervention group as compared to the control group.• To assess peak aerobic capacity (VO_2_peak) and objectively measured physical activity at six and 12 months in the intervention group as compared to the control group.• To compare changes in 24 h ambulatory blood pressure measurement and blood pressure variability at six and 12 months in the intervention group and the control group.• To compare changes in vision-related quality of life at six and 12 months in the intervention group and the control group.• To compare changes in questionnaire-derived ocular surface disease index and dry eye disease symptoms in the intervention group and the control group.

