#### Exclusion criteria

Patients eligible for this study must not meet any of the following criteria: having had glaucoma surgery within 6 months before start of the project; changes in topical medication or laser trabeculoplasty within 3 months before start of the project; severe glaucoma (visual field mean deviation lower than −12Db); eye disease that has a significant impact on the visual field; life-threatening arrhythmia, aberrant CPET (e.g., signs of ischemia) which precludes participation in an exercise trial; insulin-treated diabetes, chronic obstructive pulmonary disease or cancer; mental, clinical or physical limitation precluding safe participation in a high intensity exercise program. Subjects that perform more than 150 min of moderate to vigorous physical activity per week as defined by the Physical Activity Vital Sign questionnaire are also excluded (Kuntz et al., 2021). All participants considered for study participation, per the above criteria, will be documented on the Screening Log, including screening failures.

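### Baseline-corrected linear ANCOVA is assigned to the secondary endpoints without exception by type, which does not suit the yes/no endpoint of laser or surgery

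*Protocol article*

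**What the plan says.** **Method.** Data analysis states: "To analyze intervention effects after 6 months, we will use an analysis of covariance (ANCOVA) according to the intention-to-treat principle". The sentence continues with its scope, "to compare differences in primary and secondary endpoints between HIIT and control group", and its adjustment, "corrected for the corresponding baseline value and main confounders". No other between-group model is named.

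**Endpoint.** The Secondary objectives include IOP, use of eye drops, and "occurrence of laser trabeculoplasty or surgical interventions after six and 12 months in the intervention group as compared to the control group". The last is yes/no and the number of drops is a small count. The same list includes inflammation in peripheral blood; Blood and urine sampling names hs-CRP, IL-6 and TNF-alpha.

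**Eligibility.** The Exclusion criteria rule out "having had glaucoma surgery within 6 months before start of the project" and "changes in topical medication or laser trabeculoplasty within 3 months before start of the project".

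**Therapy changes.** Data analysis says the analysis must correct for changes in glaucoma therapy and that these enter as separate variables. A step-up (surgery, laser or added drops) "will be coded as a binary, summarizing variable (yes/no) and as separate variable", the latter counting drops and surgeries.

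**Checks.** Shapiro-Wilk tests and residual plots are planned. The article does not say what follows if either fails.

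**The concern.** The article does more than leave the binary endpoint to a later document: it assigns a method to it. Three features of that method fit badly.

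1. A normal-error, equal-variance linear model describes a 0/1 outcome poorly, above all if events are few.
2. The required baseline term has no usable content if it means recent laser or surgery. Lifetime history could vary, but the article does not define it as the baseline.
3. The therapy-change covariates include the very events that make up this endpoint. For number of drops, the covariate may be the endpoint itself.

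At stake is the reading of clinical endpoints that the Discussion presents as disease-specific. A smaller matter of the same kind is the raw-scale analysis of the inflammatory markers, which loses power if they are right-skewed.

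**Working it through.** **1. The plan's own ANCOVA figure.** The FMD calculation (Sample size calculation) gives SD 3%, r = 0.6, 62 per group and 10% dropout, so 62 × 0.9 ≈ 56 per group. The detectable difference is (z for two-sided 0.05 + z for power) × SD × √(1 − r²) × √(2/n).

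- 80% power: 2.802 × 3 × 0.8 × √(2/56) = 1.27%
- 90% power: 3.242 × 3 × 0.8 × √(2/56) = 1.47%
- r = 0, 80% power: 2.802 × 3 × √(2/56) = 1.59%

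The article states about 1.3%, 1.5% and 1.6%. These agree, so ANCOVA is sound where the outcome is continuous.

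**2. Baseline term.** Take 128 participants with an intercept, an arm indicator and a recent-history column. By eligibility that column is all zeros, and the design has rank 2 of 3. Its coefficient cannot be estimated. Software would drop it and leave the arm estimate unchanged, so the stated adjustment is empty rather than harmful.

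**3. Therapy-change covariates.** Anyone with laser or surgery during follow-up has step-up = yes. Anyone with step-up = no has outcome 0 by construction. Conditional on step-up, the arm coefficient no longer compares how often laser or surgery occurs. It compares what share of step-ups were laser or surgery rather than drops. If total drops is both outcome and covariate, the model fits exactly with coefficient 1 on the covariate and 0 on arm.

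**4. Type I error of the linear model on a 0/1 outcome.** Inputs: 128 randomised 1:1 (64 per arm), two-sided 0.05. The article gives no event rate, so 1% to 20% is an assumed range. The test is t = (p₁ − p₂)/√(s² × 2/n), with s² = n[p₁(1 − p₁) + p₂(1 − p₂)]/(2n − 2). All tables were enumerated:

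| Assumed event rate | Linear | Fisher |
|---|---|---|
| 1% | 0.004 | 0.000 |
| 2% | 0.022 | 0.001 |
| 3% | 0.038 | 0.004 |
| 5% | 0.047 | 0.012 |
| 10% | 0.051 | 0.023 |
| 20% | 0.048 | 0.030 |

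With 56 per arm the largest linear value is 0.052. A 20,000-run simulation with three added covariates and 50 v 60 completers gives 0.015 to 0.049 at rates of 2% to 10%.

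**5. Single sparse tables, 64 per arm (p-values).**

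| Events | Linear | Score | Fisher |
|---|---|---|---|
| 4 v 0 | 0.043 | 0.042 | 0.119 |
| 6 v 1 | 0.053 | 0.052 | 0.115 |
| 7 v 1 | 0.029 | 0.029 | 0.062 |
| 8 v 2 | 0.049 | 0.048 | 0.096 |

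For 4 v 0: s² = 64 × 0.0625 × 0.9375/126 = 0.0298, so t = 0.0625/√(0.0298 × 2/64) = 2.05 and p = 0.043. The linear and score tests nearly coincide, so the gap to Fisher mostly reflects Fisher's conservatism.

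**6. Skewed markers.** Assumptions: log-normal marker, log-SD 0.5 to 1.1, 56 per arm, pre-post correlation 0.6, and an effect set to give about 80% power on the log scale. Simulated power of raw-scale ANCOVA falls from about 0.72 (log-SD 0.5) to about 0.51 (log-SD 1.1). On the log scale it is about 0.79 throughout.

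**The case against.** A reader might infer that the linear model will produce false significance for laser or surgery. The documents do not support this. Under 1:1 allocation the overall error stays near or below 0.05, and well below it if events are truly rare. Given a fixed total number of events it does exceed 5% for some totals (0.119 at 4, 0.096 at 10), but it lies below 5% for others (3, 6, 7, 9, 12). A score test, which would be an acceptable replacement, gives almost the same p-values. Rarity is itself an assumption.

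It can also be said that a condensed article leaves endpoint-specific models to the analysis plan, and that the planned boxplots suggest the authors had continuous measures in mind. That lowers the weight of the point but does not remove it, because the sentence as printed covers secondary endpoints and excludes none. It does concern 6 months only; the article fixes no 12-month method, and none is criticised here.

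On the baseline, lifetime history could supply a varying covariate. True, but the article does not choose it. On the therapy-change variables, the authors may have meant them only for the vascular endpoints; the text does not say so. That the inflammatory markers are skewed is not stated in the article. It stands here as an assumption, and what to do about it is a suggestion.

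**Conclusion.** The point holds in a limited form. As written, baseline-corrected ANCOVA at 6 months applies to a yes/no endpoint for which the model is unsuitable, the recent-history baseline is constant, and the therapy-change covariates overlap with the outcome. The overlap is the most consequential of the three, because it changes what the arm coefficient estimates; it rests on a literal reading of the covariate sentences. There is no general inflation of type I error (0.004 to 0.051 with 64 per arm at assumed rates of 1% to 20%). For skewed markers the cost is power, under the assumed log-normal model. The flicker-dilation and FMD analyses are unaffected. Importance is low to moderate: worth correcting, not a threat to the trial's main result.

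**What to change.** In Data analysis or the statistical analysis plan, before any unblinded analysis:

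- Limit ANCOVA to continuous endpoints.
- Occurrence of laser or surgery: report events per arm and a risk difference with an exact or score interval, or use Firth logistic regression with site. Omit the constant baseline and the therapy step-up covariates.
- Number of drops: use an ordinal or count model adjusted for baseline number, without the step-up covariates.
- hs-CRP, IL-6 and TNF-alpha: pre-specify ANCOVA on the log scale with ratios of geometric means, stating right skew as an assumption.
- Say which endpoints the therapy-change variables are meant for.

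The cost is a few lines of text. No new data, visits or participants are needed.

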### Sample size calculation

Retinal microcirculation: Our sample size calculations were based on the regression coefficient for the group indicator (HIIT vs. CG) in an ANCOVA as described above. Our calculations were informed by the published standard errors for these coefficients of comparable trials and analyses. Specifically, we assumed a standard error of 0.23 for maximal aFID (Streese et al., 2020a) and of 0.0051 for AVR (Streese et al., 2020b). To detect adjusted group differences of 0.51% for maximal aFID and 0.03 for AVR with a power of 80%, a total sample size of 112 and 20 is required, respectively. We therefore envisage at least 112 completed participations in the study.

In case we would not meet our sample size target, we also calculated the minimum detectable β for a range of sample sizes. In case of recruitment, for example, of only 90 patients, the minimum detectable β for maximal aFID would be about 0.60% exercise-induced dilation change for a power of 0.8, and the minimum detectable β for AVR would be in the range of 0.014 exercise-induced change in ratio. These would still reflect very achievable and clinically relevant improvements of retinal microvascular health, putting the expected effects into perspective of our normative data and previously reported exercise efficacy.

Large artery function: An additional sample size calculation was performed based on the given sample size from the previous power calculation for the retinal endpoint. Our detectable group difference calculations were based on an assumed correlation coefficient of r = 0.6 between pre- and post-measurement, a standard deviation of 3%, a given total sample size of n = 124 (62 per group; MCT/HIIT group) and a dropout rate of 10%. Our calculations were informed by the published standard deviation for these coefficients of comparable trials and analyses (Lenth, 2001; Moriguchi et al., 2005; Luk et al., 2012; Ras et al., 2013; Heiss et al., 2023). With n = 62 per group and an assumption of r = 0.6 between pre- and post-measurement, we have 80% power to detect group differences in FMD of about 1.3% or larger and 90% power to detect group differences in FMD of about 1.5% or larger. We therefore target a sample size of 124 participants for the study.

If the correlation between pre- and post-measurement does not reach r = 0.6, we could still detect group differences in FMD of 1.6% with 80% power in the worst case. This would still reflect very achievable and clinically meaningful improvements in large artery function, putting the expected effects into perspective of recently published reference ranges and serve as a target for further and more tailored cardiovascular risk stratification and prevention (Luk et al., 2012; Heiss et al., 2023).

#### Data management

Data management will be performed by experienced data scientists in compliance with the guidelines of good clinical practice in collaboration with the Clinical Trial Unit (CTU) of the University of Basel and the Clinical Trial Center (CTC) of the University Hospitals UZ Leuven. The same electronic case report form (eCRF) (RedCap) is used in both centers. For personal and sensitive data, we abide the General Data Protection Regulation 2016/67 and US FDA Good Clinical Practice guidelines. Different data sources will be collected. Patient data will be digitally recorded in the form of questionnaires, clinical examination reports and image files. The management includes consistency checks of data input. Personal data and findings of this survey will be digitally stored in an encrypted format and will be used exclusively for the study. Neither names nor initials, complete birth dates or other identifiers will be included in the encrypted code (pseudonomization). After data acquisition is completed, all statistical analyses will be performed solely with pseudonomized data sets. Pseudonomized data (numeric database) will be sent from Leuven to the coordinating center. Non-disclosure to third parties, as well as other restrictions, are stipulated in the informed consent form. After the study, the data will be filed in the archive of the DSBG and in KU Leuven servers dedicated to the Research Group of Ophthalmology. The Data Management Plan has been approved by the institutional research governance committees and ethics review authorities.

## Discussion

HIT-GLAUCOMA aims to establish exercise treatment as a viable new adjunct therapy modality for glaucoma. The results of the study have the potential to enforce a paradigm shift in the treatment of patients with glaucoma by additionally applying exercise treatment. Exercise treatment has the potential to improve microvascular endothelial function, improve ocular perfusion and induce anti-inflammatory as well as anti-oxidative capacities. Glaucoma could potentially be seen, at least in part, a sequel of systemic dysfunctional pathways and theoretical microvascular dysfunction. Exercise is a much underused and readily available treatment strategy with great potential as add on treatment on top of usual care.

This is, first and foremost, a clinical study elaborating on the potential exercise-induced mechanisms of treatment effects. Nonetheless, the study investigates local retinal as well as systemic pathophysiological and molecular mechanisms that may be involved in the exercise-induced amelioration of disease progression. In many ways, this is a comprehensive and highly innovative approach combining exercise and preventive medicine as well as retinal microvascular pathophysiology with clinical ophthalmology with the potential to set new standards and offer new options for the current treatment approaches in glaucoma.

The objectives of the HIT-GLAUCOMA study are primarily to investigate intermediate endpoints such as local retinal microvascular dysfunction and systemic vascular plasticity, inflammation, and oxidative stress. These are key pathological features within the etiology of glaucoma and describe local and systemic mechanisms that impact disease progression. We aim to demonstrate the efficacy of exercise as add-on treatment on these disease entities with the potential to help stabilize the disease and reduce glaucoma-associated CV risk. The aim and concept of the study is summarized in Figure 3. The study also investigates the effects of exercise on disease specific clinical endpoints such as visual field and OCT indices, IOP, use of IOP lowering eye drops or necessity for laser trabeculoplasty or surgical intervention as well as vision related quality of life and symptomatology of ocular surface disease. As the initial phase of the study is too short for robust and reliable study of glaucoma progression in terms of visual field and OCT, longer-term follow-up is ensured to assess these changes over a longer period. The first patients are scheduled in February 2024.

**FIGURE 3 F3:**
[figure not shown]
Visual representation of the study concept on the effects of exercise training on glaucoma progression and cardiovascular risk via local and systemic disease mechanisms.

In conclusion, the comprehensive HIT-GLAUCOMA study approach will set the grounds for a new add-on exercise treatment regime for glaucoma and represents a blueprint of exercise study in all kinds of (micro)vascular diseases. Additionally, it will mobilize patients and benefit associated CV comorbidities. Exercise and its prescription could be considered an effective polypill for the treatment of systemic CV disease and may likewise prove to be an effective treatment strategy of glaucoma as a chronic smoldering neurodegenerative disease.

## Data Availability

The original contributions presented in the study are included in the article/Supplementary material, further inquiries can be directed to the corresponding authors.
